### Eligibility criteria

3.2

We will enroll 40 MS patients affected by gait disturbances and moderate-severe spasticity: 20 of them in treatment with Sativex (Group A) considered as responders, and 20 treated only with the most common antispastics used in MS (Group B). Inclusion criteria are: age range 18 to 65 years; diagnosis of definite relapsing-remitting or primary-progressive or secondary-progressive multiple sclerosis; absence of clinical relapses from no gadolinium-enhanced lesions on brain and spinal cord MRI performed at least 6 months before study entry; no mood or sleep disorders with an Hamilton score of ≤17; a moderate to severe spasticity in at least 2 districts of upper and/or lower limbs; absence of clinical or neuroradiological relapses from at least 6 months before study entry; Expanded Disability Status Scale (EDSS) total score between 3.5 and 7.0; no history of psychosis; no presence of pace-maker, aneurysms clips, neurostimulator or brain/subdural electrodes (safety TMS procedure); right handedness, central conduction time in upper limbs of <8 ms; no robotic gait training contraindications.

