### Study population

3.6

All the 40 subjects, divided into 2 groups (A: Sativex + Lokomat Training, and B: other antispastics + Lokomat training) will perform a RAGT (each session will last at least 45 minutes, 3 times per week, for a total of 20 sessions).

All the patients will undergo a complete physical and neurological examination, including the evaluation of disability by means of the EDSS, the assessment of spasticity using the Modified Ashworth Scale (MAS), and the numerical rating scale (NRS). To clarify the role of Sativex in improving spasticity gait-related symptoms, we will also administer the following scales: 10 meters walking test (10WT) and Ambulation Index (AI). Quality of life will be evaluated by means of MS quality of life 54 (MSQOL-54). The skilled clinician will be blind to the drug treatment. Moreover, we will evaluate some electrophysiological parameters to test cortical excitability: motor-evoked potentials (MEP) amplitude, short intracortical inhibition (SICI) and facilitation (ICF) from the abductor pollicis brevis muscle (APB) of the most affected side. The same assessment will be applied at baseline, at the end of the RAGT (T1), and 30 days after the end of the neurorehabilitation training (T2).

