### Study drug

3.7

Patients in treatment with Sativex will receive cannabis-based medicine extract presented in a pump action sublingual spray. Sativex is composed of whole cannabis plant extract, containing THC (27 mg/mL) and CBD (25 mg/mL), in ethanol/propylene glycol (50:50) excipient. Each actuation delivers 100 KL of spray, containing THC 2.7 mg and CBD 2.5 mg.

Sativex is indicated as treatment for symptom improvement in adult patients with moderate to severe spasticity due to MS, who have not responded adequately to other antispasticity medication and who demonstrate clinically significant improvement in spasticity-related symptoms during an initial trial of therapy (4 weeks). The drug is intended to be taken with another antispastic medication, and treatment should be started under the supervision of a doctor skilled in MS. The number and frequency of dosing (sprays) with Sativex will vary and the correct dose of Sativex for the individual patient might be reached over a couple of weeks. The most common side effects or adverse effects associated with the first 4 weeks of treatment with Sativex in clinical studies of the drug were dizziness (occurring mostly during the early stages of treatment when the dose is titrated) and fatigue. During the initial Sativex titration period, it is necessary to gradually increase the number of sprays that you take per day. You should leave at least 15 minutes between sprays and should not exceed 12 sprays per day.

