#### Visit 3 (1 month after the last robotic-rehabilitative session)

3.11.4

FIM, MAs, NRS, 10mW, 6MW, HRSD, and MSQOL 54. Muscular stiffness and strength will be evaluated by means of instrumental measures furnished by the neurorobotic device itself. Neurophysiological measure will be also assessed.

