### Statistical analysis

3.13

The Wilcoxon signed ranks test on the T0-T1-T2 differences concerning the different clinical outcome measures (EDSS, FIM, MAs, 10mW, 6MW, HSD, MSQOL 54) will be carried out in both groups. The α-level for significance will be set at *P* < 0.05. The Bonferroni correction will be used in multiple comparisons. Data will be expressed as mean or percentage ± standard deviation. The effects of the treatment on RMT, peak-to-peak MEP amplitude, SICI, and ICF will be evaluated in separate repeated-measures analyses of variance (rmANOVA). For each dependent variable, we will compute a 2-way rmANOVA with time (4 levels: T_0_- T_1_-T_2_) and group (2 levels: group A and group B) as within-subject factors. Conditional on a significant F value, post-hoc paired-sample *t* tests were performed to explore the strength of main effects and the patterns of interaction between experimental factors. The Greenhouse-Geisser method will be used if necessary to correct for nonsphericity. All data will be given as means or percent ± standard error. We also will calculate a Fisher Z-transformation concerning the correlations between clinical and electrophysiological parameters.

This is a pilot study. The main aim is to provide evidence which could allow planning of a further confirmatory study. The simple size of 40 patients was determined on the basis of feasibility criteria. Consequently, no formal statistical hypothesis was done

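### Classical repeated-measures ANOVA for the TMS outcomes uses only patients with all three visits; a mixed model would keep the observed data, a minor and cheap improvement

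*Protocol article*

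**What the plan says.** Section 3.13 (Statistical analysis) fixes the method for the four TMS outcomes (RMT, peak-to-peak MEP amplitude, SICI and ICF): they "will be evaluated in separate repeated-measures analyses of variance (rmANOVA"). The factors are "time (4 levels: T_0_- T_1_-T_2_) and group (2 levels: group A and group B) as within-subject factors". The next sentences add post-hoc paired t tests and state that "The Greenhouse-Geisser method will be used if necessary to correct for nonsphericity". A sphericity correction belongs to the classical univariate form of the analysis.

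TMS is scheduled three times. Section 3.6 says "The same assessment will be applied at baseline, at the end of the RAGT (T1), and 30 days after the end" of training (T2), and the entry for Visit 3 in section 3.11.4 repeats that "Neurophysiological measure will be also assessed". Section 3.2 sets the size: "We will enroll 40 MS patients affected by gait disturbances and moderate-severe spasticity", of whom "20 of them in treatment with Sativex (Group A) considered as responders, and 20 treated only with the most common antispastics" (Group B). The article states no dropout rate, no dropout allowance, no imputation and no mixed model.

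**The concern.** Classical repeated-measures ANOVA works on a full set of visits per patient. Someone seen at T0 and T1 but not 30 days after training contributes nothing, although two of the three values are in hand. The clinical scales in section 3.13 get Wilcoxon signed-rank tests carried out in each group, so the TMS analysis is the only one described with a group-by-time term. With 20 per group there is little to spare.

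Two things are at stake. The first is precision: the contrast between groups in change from baseline is estimated from fewer patients than were measured. The second is bias: if missing T2 depends on the T1 result, removing those patients distorts even the T1 contrast, although T1 was observed. A likelihood-based mixed model uses the observed T1 values and remains valid under missing at random.

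The complaint is not that the article is silent on missing data, which an article may leave to a fuller plan. It is that the method it does name discards observed data.

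**Working it through.** **Inputs from the article.** 20 patients per group (3.2); visits T0, T1 and T2 (3.6, 3.11); classical rmANOVA with Greenhouse-Geisser (3.13).

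**Assumptions, because the article gives no figures.** Loss per post-baseline visit m = 5, 10 or 15%; compound symmetry with unit variance and correlation 0.5; values missing completely at random. Two patterns are compared: isolated misses (T1 and T2 missed independently) and permanent dropout (a patient who leaves does not return).

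**Complete cases.** Under both patterns the expected number per group is 20(1 - m)²:
- 5%: 20 × 0.95² = 18.1
- 10%: 20 × 0.90² = 16.2
- 15%: 20 × 0.85² = 14.5 (14.45)

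**Variance of the mean change within a group.** With complete cases it is 2(1 - 0.5)/n = 1/n. For the mixed model, the inverse covariance of the visits observed is summed over patients, the sum is inverted, and the variance of T1-T0 or T2-T0 is read off. Both groups have the same expected pattern, so the ratio for the between-group contrast equals the ratio within a group.

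Worked case, 10% isolated misses, per group: 16.2 complete, 1.8 without T1 only, 1.8 without T2 only, 0.2 with baseline only. A complete patient contributes 1.5 on the diagonal and -0.5 off it; a two-visit patient 4/3 and -2/3; a baseline-only patient 1.
- T0 diagonal: 16.2 × 1.5 + 3.6 × 4/3 + 0.2 = 29.3
- T1 and T2 diagonals: 16.2 × 1.5 + 1.8 × 4/3 = 26.7
- T0-T1 and T0-T2: -8.1 - 1.2 = -9.3; T1-T2: -8.1

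Inverting gives a variance of 0.05375 for T1-T0. Complete cases give 1/16.2 = 0.06173. The ratio is 0.06173/0.05375 = 1.148.

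**Complete-case variance relative to the mixed model:**

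| Loss per visit | Isolated misses, either contrast | Permanent dropout, T1-T0 | Permanent dropout, T2-T0 |
|---|---|---|---|
| 5% | 1.070 | 1.07 | 1.03 |
| 10% | 1.148 | 1.14 | 1.06 |
| 15% | 1.236 | 1.22 | 1.09 |

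**Power for the interaction.** The 0.61 in section 3.12 has no stated metric; here it is taken, as an assumption, to be a group difference of 0.61 SD at both T1 and T2. Noncentral F, two numerator degrees of freedom, alpha 0.05:
- rmANOVA on complete cases: 44, 40 and 36% at 5, 10 and 15% loss.
- Mixed model, permanent dropout, about 37 denominator degrees of freedom (an approximation to unstructured covariance with Kenward-Roger): 45, 43 and 41%.
- No missing data: 48% for rmANOVA (76 denominator degrees of freedom) and about 47% for the mixed model.

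In this setting the gain is about 1, 3 and 5 points, and with complete data the mixed model costs about one point. The 36 per group in section 3.12 does not enter this comparison.

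**The case against.** The strongest reply is that section 3.13 names a test and no exclusion rule. The article is condensed, and a fuller plan could add imputation. That stands in part: the exclusion follows from the method and is not stated in words, and the loss may turn out to be nil. It does not remove the point, because a plan that applies the analysis as written inherits the restriction.

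The study is also a pilot whose 40 patients were set by feasibility, with no formal hypothesis, and power is below 50% by either method. rmANOVA is an accepted technique. This stands, and it limits the weight of the point.

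A reader might infer that missed visits will be commoner in Group A, because section 3.7 lists "dizziness (occurring mostly during the early stages of treatment when the dose is titrated) and fatigue" among the effects of Sativex, and might attach a bias to it: if exactly the 20% of Group A with the worst T1 change all skipped T2, the complete-case T1 change would shift by 0.35 SD. The article does not support this. Section 3.7 refers to the first 4 weeks of treatment and places the dizziness mostly in titration, while section 3.4 admits Group A only after one month on Sativex and only as responders. Patients who tolerated it badly would mostly have gone before T0. The 0.35 SD is a deterministic extreme, not an expectation.

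Finally, Group A is selected on response after randomisation (3.4), so a mixed model does not restore comparability between the groups. That is a separate problem.

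**Conclusion.** The point holds as a minor improvement. As written, and with no imputation stated, the TMS analysis uses only patients with all of T0, T1 and T2 and discards observed values from the rest. At 5 to 15% loss per post-baseline visit the variance penalty is about 7 to 24% with isolated misses. With permanent dropout it is about 7 to 22% for T1-T0 and 3 to 9% for T2-T0. The power difference runs from about one point to several.

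These sizes rest on assumed dropout rates, compound symmetry and a correlation of 0.5, and they fall to zero if every visit is complete. Bias in the T1 contrast is possible if missing T2 depends on the T1 result, but nothing in the article shows that this will happen or that it would differ between groups.

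**What to change.** In section 3.13, replace the rmANOVA with a linear mixed model for each TMS outcome: group as a between-patient factor, visit with three levels (T0, T1, T2), the group-by-visit interaction, unstructured within-patient covariance, REML with Kenward-Roger degrees of freedom, and all observed visits included. The same edit corrects two slips in the present sentence, which calls group a within-subject factor in a parallel-group trial and states four time levels while naming three. Keep the Greenhouse-Geisser sentence only if a complete-case rmANOVA is retained as a sensitivity analysis.

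The cost is a few sentences and standard software, with no new data. The downsides are slightly fewer denominator degrees of freedom when data are complete, and reliance on missing at random.

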### Trial design

3.1

This is a rater-blinded, active-controlled, parallel-group pilot study to assess the efficacy of Sativex associated with robotic-rehabilitation in improving the motor performances of Multiple Sclerosis patients. This study will be conducted at the IRCCS Centro Neurolesi Bonino-Pulejo in Messina, Italy. The study protocol was approved by the Ethical and Research Committee of IRCCS Centro Neurolesi Bonino-Pulejo (13/2016 vers, n 1 23/11/2016). The trial is registered under trial gov. (NCT03186664). The study purpose will be explained to the participants, and patients’ consent will be obtained before the enrollment by the principle investigator.

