### Randomization of participants

3.5

The subjects were randomly assigned to one of the two treatment groups, using a simple randomization scheme generated by a software (www.randomization.com). Individual, sequentially numbered index cards with the random assignments were prepared. The index cards were folded, and placed in sealed opaque envelopes

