#### Pre-screening Visit

3.11.1

Evaluation of inclusion and exclusion criteria. Signature of informed consent.

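### The TMS repeated-measures ANOVA makes group a within-subject factor and gives time four levels, in a parallel-group trial with three assessments

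*Protocol article*

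**What the plan says.** **Model (Statistical analysis, 3.13).** RMT, peak-to-peak MEP amplitude, SICI and ICF are each analysed in a two-way repeated-measures ANOVA. Time is given four levels, although the labels listed are T0, T1 and T2. The sentence then adds "and group (2 levels: group A and group B) as within-subject factors". The plural covers both terms, so group is declared within-subject.

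**Follow-up tests (same section).** "Conditional on a significant F value, post-hoc paired-sample" t tests are to explore the main effects and the pattern of the interaction. The text does not say which contrasts they cover.

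**Design.** Trial design (3.1): "This is a rater-blinded, active-controlled, parallel-group pilot study". Randomization of participants (3.5): "The subjects were randomly assigned to one of the two treatment groups, using a simple randomization scheme". Study population (3.6) divides the 40 patients into A and B. No crossover or matching is described.

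**Assessments.** Study population (3.6): "The same assessment will be applied at baseline, at the end of the RAGT (T1), and 30 days after the end of the neurorehabilitation training". The timeline agrees, with visits 1, 2 and 3 each listing the neurophysiological measures. The pre-screening visit contains only this: "Evaluation of inclusion and exclusion criteria. Signature of informed consent".

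**Sample size (3.12).** The inputs include four repeated measurements.

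**The concern.** A within-subject factor is one that each patient experiences at every level. No patient here is measured in both groups, so group can only be a between-subject factor, and the written model does not describe the data that will be collected.

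This is the only analysis in the article with a group term; the Wilcoxon signed-rank tests on the clinical scales look at change over time in each group. It therefore carries the article's one stated comparison of Sativex with control, on cortical excitability. If the sentence is followed literally, the group and group-by-time tests use the wrong error term and depend on an arbitrary choice. The paired follow-up tests carry the same fault into any A-versus-B contrast.

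**Working it through.** **1. Levels of time.** The plan states 4. The assessments that include TMS are baseline (T0), end of robotic training (T1) and 30 days later (T2), which makes 3. Pre-screening covers eligibility and consent only, so it supplies no fourth level. The stated 4 is not reproduced. Because the Sample size section repeats it, the error sits in two places.

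**2. Degrees of freedom.** Inputs: n = 20 per group, N = 40 (Eligibility criteria), m = 3 times.

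| Test | Group between-subject (mixed design) | Group within-subject (as written) |
|---|---|---|
| Group, error df | N − 2 = 40 − 2 = 38 | n − 1 = 20 − 1 = 19 |
| Group × time, error df | (N − 2)(m − 1) = 38 × 2 = 76 | (n − 1)(m − 1) = 19 × 2 = 38 |
| One A-versus-B t test, df | N − 2 = 38 | n − 1 = 19 |

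With the stated four levels, the interaction error df would be 19 × 3 = 57 as written, against 38 × 3 = 114 in a mixed design.

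**3. What running the model requires.** Keyed by patient, every patient has data at one level of group only, so a within-subject group effect cannot be estimated. The model runs only if an A patient and a B patient are set side by side as one case. It then works on differences D = A − B. The group means at each time do not depend on who is paired with whom, but the spread of D does. The numerator of F is therefore fixed and the denominator changes with the pairing. If dropout leaves the arms unequal, the surplus patients have no partner and fall out.

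**4. How far p can move in one dataset.** One dataset was simulated with 20 + 20 patients, three times, correlation 0.5 and a shift of 0.61 SD at T1 and T2 (all assumed), then re-paired 5000 times:

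- Group: p from 0.012 to 0.27 (central 95% of pairings 0.058 to 0.23); mixed design p = 0.14.
- Group × time: p from 0.33 to 0.72 (central 95% 0.48 to 0.68); mixed design p = 0.60.

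**5. Long-run behaviour.** Under the same assumptions, in 4000 simulated trials at nominal 5%:

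| | Mixed design | As written |
|---|---|---|
| Type I error, group × time | 5.7% | 5.8% |
| Type I error, group | 5.3% | 4.9% |
| Power, group × time | 48% | 46% |
| Power, group | 34% | 33% |

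**6. How often one pairing changes the conclusion.** With assumed correlation 0.6 and effects of 0.61 SD at T1 and 0.45 SD at T2, a single arbitrary pairing and the mixed design fall on different sides of 0.05 for group × time in about 6 to 7% of trials. With no effect the figure is about 2%. Over correlations from 0.3 to 0.8 and effects from zero to 1.0/0.8 SD, it runs from 0% to 7%.

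**7. Paired t tests.** T0 against T1 or T2 within one group compares a patient with himself or herself, so pairing is right. A against B at a given time compares different patients, so it is not.

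**The case against.** The strongest reply is that the practical harm is small. An arbitrary pairing unrelated to the outcomes leaves type I error near nominal and costs about two points of power. The trial is declared a pilot, sized for feasibility and without a formal hypothesis. The analysis covers neurophysiology only, and the Wilcoxon tests on the clinical scales are untouched. Anyone who enters the data by patient will also find that the model cannot be fitted and will probably notice the slip. All of this stands, and it limits the severity. It does not make the sentence right: the article fixes a particular model, so this is not detail left to a fuller document.

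Three stronger readings are tempting and are not supported:

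- *That the tests are biased or reject too often.* Step 5 shows no inflation.
- *That about a third of trials would change their conclusion.* Under the step 6 inputs, significance of the interaction does depend on pairing in about 35% of trials when 50 pairings are tried. That count rises with the number tried (9% with 2, 26% with 10, 45% with 400). A trial is analysed once, so the single-pairing figure is the relevant one.
- *That paired t tests are wrong altogether.* They are right over time within a group, and the section does not say that they will be used for A versus B. The fault is that it does not separate the two uses.

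**Conclusion.** The point holds as an error of specification. Group cannot be a within-subject factor in this design, and time has three levels, not four. Both follow from the article's own text and need no assumption. The loss of error df (38 to 19 for group, 76 to 38 for group × time) follows from 20 + 20 patients and three times.

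The consequence is a p-value that is not unique and an analysis that cannot keep unpaired patients. It is not a distorted error rate. The 6 to 7% disagreement rests on an assumed correlation and assumed effect sizes: the article gives 0.61 without a metric and gives no correlation. The text should be corrected because it is wrong as written, but in an exploratory pilot analysis of neurophysiology this is not a threat to the trial's overall conclusions.

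**What to change.** In Statistical analysis, specify for each TMS variable a mixed-design ANOVA or a linear mixed model, with time as the within-subject factor (three levels: T0, T1, T2), group as the between-subject factor, and group × time as the test of interest. State that follow-up contrasts between groups are independent-sample or T0-adjusted, and that paired contrasts are used only over time within a group.

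In Sample size, change the number of repeated measurements to three, to match. The effect of that change on the calculated 36 per group cannot be worked out from the article, which omits the effect-size metric, the sidedness and the correlation; the calculation should be redone from its source or marked as not governing the chosen 40.

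The cost is a few sentences of wording, plus that recalculation if it is kept. No visit, measurement or patient is added.

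### For the TMS outcomes, the post-hoc rule does not name the F test that opens it and offers only paired tests, so it permits a change in group A alone to be read as a Sativex effect when the interaction is null

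*Protocol article*

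**What the plan says.** Section 3.13 (Statistical analysis) applies a separate repeated-measures ANOVA to each neurophysiological outcome: "The effects of the treatment on RMT, peak-to-peak MEP amplitude, SICI, and ICF will be evaluated" in this way. The factors are time and "group (2 levels: group A and group B) as within-subject factors". The follow-up rule begins "Conditional on a significant F value, post-hoc paired-sample" and continues with t tests whose purpose is "to explore the strength of main effects and the patterns of interaction between experimental factors". No other follow-up of these ANOVAs is given.

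The same section sets the level ("The α-level for significance will be set at *P* < 0.05") and adds "The Bonferroni correction will be used in multiple comparisons", without saying which comparisons form a family.

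Section 3.6 (Study population) gives both groups the robotic training: "A: Sativex + Lokomat Training, and B: other antispastics + Lokomat training) will perform a RAGT". It schedules three assessments: baseline, end of training (T1) and 30 days later (T2). Section 3.12 (Sample size) names the interaction as the effect its calculation was meant to detect.

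**The concern.** A time-by-group ANOVA gives three F tests: time, group, and time by group. Only the last asks whether the two groups changed differently. The rule names none of them, and by including main effects among the things to be explored it implies that a main-effect F is enough to start the follow-up.

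Both groups train on the Lokomat, so the time F can be significant with no contribution from Sativex. The paired tests are then available, and they are also the only tool offered for describing an interaction. They cannot do that job directly. A and B are different people, so a paired test compares visits either within one group or in all patients pooled. A pooled test says nothing about interaction. What remains is to set A's change beside B's.

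Comparing a significant result in one group with a non-significant result in the other is not a test of the difference between the groups, and it does not hold the 5% level for that difference. At stake is a false impression, on the mechanistic outcomes, that Sativex altered cortical excitability, carried into the planning of the confirmatory study.

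**Working it through.** **Plan's own figure.** Section 3.12 gives 36 per group for an interaction, with an effect size of 0.61. The metric of the effect size and the correlation between visits are not given. Read as a two-sample standardised difference, 0.61 needs 43 per group two-sided or 34 one-sided at 80% power. Interaction F-test versions give answers from 3 to 90 per group, depending on the convention. The figure can be neither confirmed nor refuted, and this point does not depend on it.

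**Inputs from the article.** 20 patients per group (section 3.2), three visits (section 3.6), level 0.05 (section 3.13).

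**Assumptions.** Two-sided tests; correlation 0.5 between any two visits; normal data; the same true change from T0 to T1 in both groups, expressed in SDs of the change and kept to T2; no Sativex effect. The article gives no expected change in the TMS measures, so a range is shown. Group is treated as between-subject, since the groups are different patients.

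**Step 1, without the gate.** Let p be the power of a paired t test in 20 patients. The chance that A is significant and B is not is p(1 − p).
- 0.3 SD: p = 0.247, so 0.247 × 0.753 = 0.186
- 0.5 SD: p = 0.565, so 0.565 × 0.435 = 0.246
- 0.7 SD: p = 0.844, so 0.844 × 0.156 = 0.132

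These ignore the F gate and are upper limits for the rule.

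**Step 2, with the gate.** Simulation of 20,000 trials per row: mixed ANOVA, then T0–T1 paired tests within each group. The literal gate is a significant time F or interaction F. The simulation error near 23% is √(0.232 × 0.768 / 20,000) = 0.3 points.

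| Shared change (SD) | Time F significant | A only, literal gate | of which interaction not significant | A only, interaction gate | A only, literal gate, paired tests at 0.05/3 |
|---|---|---|---|---|---|
| 0 | 4.9% | 1.8% | 0.8% | 1.0% | 0.9% |
| 0.2 | 23.3% | 7.0% | 5.8% | 1.3% | 4.1% |
| 0.3 | 47.2% | 13.9% | 12.3% | 1.6% | 9.7% |
| 0.4 | 72.6% | 20.8% | 18.9% | 1.8% | 16.5% |
| 0.5 | 90.3% | 23.2% | 21.5% | 1.8% | 22.6% |
| 0.6 | 97.9% | 19.4% | 17.8% | 1.6% | 24.8% |
| 0.7 | 99.7% | 13.0% | 11.6% | 1.4% | 21.3% |
| 0.8 | 100% | 7.2% | 6.4% | 0.8% | 14.6% |
| 1.0 | 100% | 1.1% | 0.9% | 0.2% | 4.1% |

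The interaction F itself rejects in about 5% of trials throughout, as it should.

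**Step 3, sensitivity.** If only half of the change is kept at T2, the 0.5 SD figure is 21.5%. Letting a significant group F open the gate as well moves the figures by at most 0.3 points. Bonferroni moves the peak to a larger shared change but does not lower it: 24.8% with three comparisons and 24.1% with six, both at 0.6 SD. At 36 per group the unadjusted peak is 22.6% (at 0.4 SD).

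**The case against.** The strongest reply is that the sentence can be read respectively: a significant main effect is followed by tests of that main effect, and a significant interaction by tests of its pattern. On that reading the pooled follow-up of time is legitimate. This stands as a possible reading, but the text does not choose it. It would also leave the interaction with paired tests only, none of which compares A with B.

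A reader might infer that the plan intends to call a change in A alone a Sativex effect. The article does not say so. It leaves that reading open, and the point goes no further. A reader might also multiply the per-outcome risk over the four TMS outcomes. That would need all four to shift by the same moderate amount and to be independent. Section 3.9 expresses SICI and ICF relative to the same unconditioned MEP from the same muscle, so no across-outcome figure is supported.

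Three further limits stand. The rule covers only the TMS outcomes. These are recorded from a hand muscle, and the article gives no size for the effect of gait training on them; if that effect is nil or very large, the problem nearly vanishes. And the study is a pilot sized on feasibility, which lowers the stakes. It still tests at 0.05, and its aim is to clarify what Sativex adds.

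The detail of follow-up contrasts may be left to an analysis plan. Here, however, the article states a rule, and the rule as stated is too loose.

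**Conclusion.** The point holds as a fault of wording and method in section 3.13, limited to RMT, MEP amplitude, SICI and ICF. The gate is unnamed, a shared time effect satisfies it literally, and the only follow-up offered cannot compare the groups.

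With no Sativex effect, the chance per outcome of an A-only pattern runs from about 2% (no shared change) up to 23% (0.5 SD, about 21 points of it with a non-significant interaction) and back to 1% (1.0 SD). With the interaction F as gate it is at most about 2%. These sizes rest on the assumed correlation of 0.5, normal data and an equal change in both groups; the true shared change is unknown. Declaring group a between-subject factor is also needed, but would not by itself cure the gate.

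**What to change.** In section 3.13, state for the TMS outcomes that:

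- group is a between-subject factor, and the group-by-time F is the test of a Sativex effect;
- group follow-up is by between-group differences in change (T1 − T0 and T2 − T0) with 95% confidence intervals, reported whatever the F and interpreted as a group effect only if the group-by-time F is significant;
- a significant time main effect is followed up on both groups combined and is not attributed to Sativex.

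This costs a few sentences and needs no further patients, visits or measurements. Reporting the differences with their intervals in every case also serves the pilot's purpose, since those are the figures needed to plan the confirmatory study.
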